### Clinical intervention and follow-up

After obtaining informed consent, axillary surgery will be omitted for eligible patients, and BCS or mastectomy (allowing breast reconstruction) will be voluntarily selected by the patient under the premise of ensuring therapeutic efficacy. Patients receiving BCS must undergo whole breast irradiation (WBI) after surgery, and postoperative adjuvant therapy and other treatments will be performed according to clinical guidelines.

Multiple timepoints will be established for dynamic follow-up at baseline and up to 3 years postoperatively, with a comprehensive and objective assessment of breast cancer-related lymphoedema (BCRL) using multi-segmental arm circumference measurements and bioelectrical impedance analysis at baseline, 1 week, 1, 3, 6, 12, 18, 24, and 36 months postoperatively, respectively. Patients will be administered a QoL questionnaire using the validated FACT-B (Version 4.0) and Quick DASH at the same time point.^30 31^ BCRL incidence and QoL will be subjectively assessed by patients using patient-reported outcomes (PROs).

Patients who discontinue or withdraw from the trial for any reason during the trial can be treated with disease-specific therapies, including supplemental SLNB, ALND, radiotherapy and other therapies as appropriate, after obtaining informed consent.

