### Postoperative radiotherapy

Adjuvant WBI with 3D conformal radiation therapy or intensity-modulated radiation therapy to the remaining breast is mandatory after BCS. The radiotherapy target area will not include the axillary region, and chest wall irradiation can be omitted with mastectomy. In this trial, either conventional fractionated radiotherapy or macrofractionated radiotherapy regimens will be used. The conventional fractionated whole breast radiotherapy dose will be 50 Grey (Gy) in 25 fractions, with a single dose of 2.0 Gy, five times per week. The tumour bed area will be selected to be added simultaneously or sequentially to DT60 Gy in 25 fractions, with a single dose of 2.4 Gy in fraction. The macro-fractionated radiotherapy whole breast radiotherapy dose will be 43.5 Gy in 15 fractions with a single dose of 2.9 Gy. The tumour bed area will be increased to 52.5 Gy in 18 fractions with a single dose of 2.9 Gy.

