##### 2. Bioelectrical impedance analysis (BIA)

The single-frequency bioimpedance analysis (SFBIA) ratio is defined as the ratio of the unaffected to the affected side.^33^ The SFBIA ratio of both upper limbs at 1 kHz and 5 kHz will be measured using bioelectrical impedance technology. The diagnostic criteria in this study will refer to the findings of Liu Miao *et al*. BCRL recognition is superior when the threshold is set at the mean+2 SD for healthy women.^34^ BCRL will be diagnosed when any one of the following is fulfilled:

The dominant affected arm SFBIA ratio at 1 kHz of >1.067.The nondominant affected arm SFBIA ratio at 1 kHz of >1.043.The dominant affected arm SFBIA ratio at 5 kHz of >1.068.The nondominant affected arm SFBIA ratio at 5 kHz of >1.044.PROs: Patients will be followed up with questionnaires using FACT-B (Version 4.0) and Quick DASH during the same period as the BCRL assessment. The FACT-B scale will be used to assess changes in QoL in breast cancer patients with SLNB omission from baseline to 3 years after surgery. The Quick DASH scale will be used to assess changes in arm morbidity from baseline to 3 years after surgery.Locoregional recurrence (LRR), local recurrence (LR), regional recurrence (RR)： LR is defined as the time from surgery to the appearance of a tumour in the ipsilateral breast, chest wall or skin at the surgical scar. RR is defined as the time from surgery to the appearance of a tumour in the lymphatic drainage area of the affected side, including the axillary, supraclavicular, subclavicular and internal mammary lymph node regions. Clinical recurrence suggested by imaging or other investigations requires a definitive diagnosis by cytology or histopathology. Suspected recurrent lesions for which histological or cytological examination is not possible will be submitted to the Data Safety Monitoring Board (DSMB) for independent review.

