### Data collection and management

This study uses an electronic case report form to manage and record the study data, and a password-protected access system will be set up to maintain participant confidentiality. The principal investigator has full responsibility of entire projects of this trial. The researchers needed to ensure that the data entry and correction were timely, complete, accurate and truthful. To ensure the accuracy of the data, double-entry and proofreading will be done independently by two data administrators. The clinical supervisor will perform data checking after the end of the study. The researcher will reply and follow-up on corrections promptly when the data are found to be incomplete inconsistent are challenged. If a subject withdraws their informed consent during participation in a clinical trial, no data will be collected after withdrawal. Study-related data collected before withdrawal will be retained and used for up to 3 years after withdrawal. At the end of the study, the principal investigator will submit a final report for review and written approval by the ethics committee.

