### Missing data and dropouts

Patients who discontinue or withdraw from the trial for any reason during the trial can be treated with disease-specific therapies and will not adversely affect their subsequent treatment, including supplemental SLNB, ALND, radiotherapy and other therapies as appropriate, after obtaining informed consent. For missing data, we will not perform any imputation. Instead, we will use the last observation carried forward method, which helps to maintain the integrity of the ITT analysis.

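### The plan does not separate a later change of axillary strategy from leaving the trial, so later iDFS events in patients who have supplemental axillary treatment can go uncounted or be scored event-free

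*Protocol article*

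**What the plan says.** All places are in the protocol article.

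- **Clinical intervention and follow-up:** "Patients who discontinue or withdraw from the trial for any reason during the trial can be treated with disease-specific therapies, including supplemental SLNB, ALND, radiotherapy". For patients in the trial, the same section says that "postoperative adjuvant therapy and other treatments will be performed according to clinical guidelines".
- **Missing data and dropouts** repeats the rule, adding that leaving "will not adversely affect their subsequent treatment, including supplemental SLNB, ALND, radiotherapy and other therapies as appropriate". It then says both that nothing will be imputed and that the last observation will be carried forward to protect the ITT analysis.
- **Postoperative radiotherapy:** whole-breast irradiation "to the remaining breast is mandatory after BCS", but "The radiotherapy target area will not include the axillary region".
- **Data collection and management:** "If a subject withdraws their informed consent during participation in a clinical trial, no data will be collected after withdrawal". Data gathered before that point are kept and used for up to 3 years.
- **Consent or assent:** the data of a participant who withdraws completely are left out of the final analysis.
- **Abstract and Statistical analysis:** the primary analysis is ITT, and the abstract includes every enrolled patient.
- **Primary endpoint:** regional recurrence is an iDFS event. The recurrence definitions, printed at the end of the bioimpedance subsection, add: "Clinical recurrence suggested by imaging or other investigations requires a definitive diagnosis by cytology or histopathology".

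**The concern.** The intervention is a single act: leaving the axilla alone at surgery. The natural later departure from it is axillary surgery or axillary irradiation. Supplemental SLNB and ALND appear in two places only, and in both the subject of the sentence is a patient leaving the trial. No section describes a patient who has later axillary treatment and stays in follow-up. The wording is to discontinue or withdraw from the trial, not from the assigned strategy, so the two are not told apart.

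This matters because such departures are unlikely to be random. A patient is more likely to change strategy when final pathology or a follow-up image raises doubt about the axilla. If her exit ends data collection, removes her from the analysis or freezes her last event-free visit, observed 3-year iDFS rises and non-inferiority is easier to claim. A single-arm trial has no control group in which the same loss would occur. Confirming pathology obtained at or after exit, and later distant events and deaths, would be lost in the same way.

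**Working it through.** **1. The plan's own figure.** From Sample size calculation: expected 3-year iDFS 90%, margin 5% (null 85%), power 80%, α 0.05, dropout 10%, N = 311. The side of the test is not stated; one-sided 0.05 is used here.

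n = [1.645·√(0.85×0.15) + 0.842·√(0.90×0.10)]² / 0.05² = 282.1, so 283. Then 283/0.9 gives 315 and 283×1.1 gives 312. An exact test first reaches 80% power at 281 and 282, and 282×1.1 gives 311. The stated figure is reproduced within rounding and choice of method.

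**2. The decision rule.** Evaluable: 311×0.9 ≈ 280. The exact one-sided 5% test of 85% rejects at 249 or more event-free, that is, at most 31 events; its actual size is 3.6%. Expected events are 28 at 90% and 42 at 85%. Only three events separate the expected count from the limit.

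**3. If switchers are deleted** (the Consent or assent rule). Let d be the share switching and r their 3-year event risk, with true iDFS 85% overall. Neither d nor r is in the documents; both are assumptions.

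Retained iDFS = 1 − (0.15 − d·r)/(1 − d). The false-claim probability is the chance of at least 249 event-free among 280 at that rate. Events unseen = 311·d·r.

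| d | r | Retained iDFS | False claim | Events unseen |
|---|---|---|---|---|
| 0 | – | 85.0% | 3.6% | 0 |
| 1% | 30% | 85.2% | 4.1% | 0.9 |
| 2% | 30% | 85.3% | 4.8% | 1.9 |
| 5% | 15% | 85.0% | 3.6% | 2.3 |
| 5% | 20% | 85.3% | 4.6% | 3.1 |
| 5% | 30% | 85.8% | 7.5% | 4.7 |
| 10% | 30% | 86.7% | 15% | 9.3 |
| 10% | 40% | 87.8% | 32% | 12.4 |

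The row at r = 15% shows no bias: deletion distorts only when switchers differ in risk from the rest.

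**4. If they are carried forward as event-free** (the Missing data and dropouts rule). Assume all their events fall after exit. Apparent iDFS = 1 − (0.15 − d·r). What matters is the share f of all true events that is hidden, f = d·r/0.15.

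| f | Example | Apparent iDFS | False claim |
|---|---|---|---|
| 5% | d = 5%, r = 15% | 85.75% | 7.2% |
| 10% | d = 5%, r = 30% | 86.5% | 13.4% |
| 20% | d = 10%, r = 30% | 88.0% | 35.7% |

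Carrying forward is the harsher mechanism: it biases the result even at average risk, because events are recorded as successes.

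**5. Which rule reaches which patient.**

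- Consent withdrawn: collection stops, but earlier data are kept (Data collection and management).
- Complete withdrawal: excluded (Consent or assent).
- Discontinued without withdrawing consent: nothing is stated on iDFS follow-up.
- Every enrolled patient: included under ITT (Abstract).

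The second and fourth statements cannot both be followed, and the third leaves open the case that matters here.

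**The case against.** The best reply is that the sentence on supplemental treatment protects patients: it assures those who leave that they lose no access to care. It says that they can have such treatment, not that having it makes a patient a leaver. This stands, and it rules out several stronger readings.

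- A reader might infer that supplemental axillary treatment is offered only to those who leave. The word only is absent, and guideline-based other treatments are open to patients who stay. What can be said is that supplemental SLNB and ALND are described only in connection with leaving, and that the axilla is outside the trial's radiotherapy target.
- A reader might infer that all such patients leave iDFS follow-up. Loss of data is explicit only for consent withdrawal and complete withdrawal. For discontinuation the article is silent, and the full protocol may cover it.
- A reader might infer that a recurrence confirmed at axillary surgery is generally missed. Table 1 schedules palpation and imaging from 3 months to 3 years. A node found and proven on study is an event, and a lesion that cannot be sampled goes to the DSMB. The event is lost only if exit comes before confirmation.
- A reader might take 15% or 32% as the expected error. Those figures assume full deletion at rates that the documents do not support. The Introduction cites 0.7% axillary recurrence at 5 years after omission, about 2 of 311 patients (0.007×311 = 2.2). Departures prompted by adverse pathology would be additional, at an unknown rate. Under Kaplan–Meier censoring, time and events before exit would also be kept.

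What the reply does not remove is the conflict over withdrawn patients, or the failure to distinguish a change of strategy from an exit.

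**Conclusion.** The point holds as a defect of wording with a possible effect on the primary endpoint. The article describes supplemental axillary surgery only for patients leaving the trial, and its rules on withdrawal, exclusion and carrying forward conflict with ITT for all enrolled. Followed as written, they can lose the later iDFS events of the patients who tell most about whether omission is safe, or score them as event-free.

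The direction favours non-inferiority if these patients are at above-average risk, or at any risk if their status is carried forward. The size cannot be fixed from the documents. With deletion and 30% risk, it is minor at 1–2% switching (up to about 1.2 percentage points above the nominal 3.6%), a doubling at 5%, and about fourfold at 10%, which would use the whole planned dropout allowance. These figures assume a one-sided exact test with 280 evaluable patients and a true iDFS of 85%.

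**What to change.** 1. Reword the sentence in Clinical intervention and follow-up and its repeat in Missing data and dropouts. Supplemental SLNB, ALND or axillary radiotherapy is recorded with date, reason and pathology, and is not in itself a discontinuation or withdrawal. Such patients stay on the Table 1 schedule and are followed for iDFS to 3 years in the ITT analysis. Pathology from the procedure counts toward the required confirmation of recurrence.
2. State that only withdrawal of consent ends data collection.
3. Reconcile Data collection and management and Consent or assent with the Abstract: data up to withdrawal are kept and the patient is censored at that point, neither excluded nor carried forward for iDFS. Censoring at true withdrawal can still be informative, so report the number and reasons.

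A withdrawal form that offers to stop visits only, and a rule dating events to first suspicion, are optional extras.

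Cost: protocol and consent wording with ethics review, and one case report form page. A few more patients continue existing visits at the single centre, and observed iDFS may be slightly lower. Enrolment is expected to run to June 2026; the change is best made early, because follow-up not collected may not be recoverable. It proposes no rule on who receives axillary treatment.

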**Methods and analysis:**

The OMSLNB trial is a prospective, single-arm, non-inferiority, phase II, open-label study design involving female breast cancer patients with a tumor of ≤3 cm in diameter, who are considered axillary lymph-node-negative based on two or more radiological examinations, including axillary lymph node ultrasonography. Eligible patients will avoid axillary surgery but will undergo breast surgery, which is not limited to breast-conserving surgery. The trial begins in 2023 and is scheduled to end in 2027. The primary endpoint is 3 year invasive disease-free survival (iDFS). The secondary endpoints include the incidence of breast cancer-related lymphoedema, patient-reported outcomes, locoregional recurrence, local recurrence and regional recurrence. It is expected that the 3 year iDFS in patients undergoing SLNB is about 90%, combined with a non-inferiority cut-off of 5%, 80% power, 95% CIs, 0.05 test level, and 10% loss to follow-up rate, the planned enrollment is 311 patients. All enrolled patients will be included in the intention-to-treat analysis.

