## Methods and analysis

### Trial design and setting

This study is a prospective, noninferiority, single-arm, phase II open-label clinical trial conducted at the First Hospital of Nanjing Medical University. Patients with unilateral invasive breast cancer (tumor ≤3 cm) and assessed as cN0 will be eligible for inclusion. The enrolled patients are required to complete two or more imaging tests, including axillary ultrasound assessed as axillary lymph-node-negative, and other tests including MRI, PET-CT and [18F]-FDG PET/MRI. Patients with suspected lymph node metastasis will be directly excluded from enrollment. All patients are required to undergo preoperative coarse needle aspiration or intraoperative mass biopsy for pathologically confirmed invasive breast cancer (regardless of pathological type). Subsequently, surgeons will be required to provide a detailed explanation of the potential benefits and risks associated with the omission of SLNB to eligible patients. Before any surgical procedure is undertaken, patients must provide written informed consent. Following consent, patients will undergo BCS or mastectomy (allowing for breast reconstruction) without axillary surgery, with a postoperative follow-up of 3 years.

This clinical study will be conducted following the relevant provisions of the Declaration of Helsinki, and it was registered at http://www.clinicaltrials.gov (NCT number: NCT05935150). The study was reported according to the Standard Protocol Items: Recommendations for Interventional Trials (SPIRIT) checklist.^29^ The detailed flow chart of the study is shown in figure 1.

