### Sample size calculation

In this study, we used PASS software (version 2021) to perform a sample size calculation for a one-proportion non-inferiority test. The sample size was based on the primary endpoint of iDFS. According to the literature exploration and previous research results, it is expected that the 3 year iDFS in patients undergoing SLNB is about 90%. We set the non-inferiority margin at 5%, with a power of 80%, a significance level (α) of 0.05 and a 95% CI. Considering a 10% dropout rate, PASS software calculated the required sample size to be 311 patients.

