### Statistical analysis

The primary analysis will use an intention-to-treat (ITT) analysis. For categorical variables, the χ2 test or Fisher’ s exact test will be used, and the data will be presented as totals, percentiles and frequencies. For continuous variables, descriptive statistics will be analysed using mean, SD or median and IQR. Independent samples t-tests will be used for normally distributed continuous variables, and nonparametric tests will be used for skewed data to analyse the results. Kaplan–Meier curves and log-rank tests will be used to determine the statistical significance of variables in the survival outcome categories (iDFS) and survival curves will be plotted. The prognostic significance of variables will be assessed using univariate and multivariate COX risk regression analyses. HR and 95% CI will be calculated. For each statistical analysis, a p value <0.05 will be considered statistically significant.

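### ITT alone lets patients who discontinue, have the axilla treated before an iDFS event and stay in the analysis count towards the non-inferiority of omitting SLNB

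*Protocol article*

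**What the plan says.** All references are to the protocol article.

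- **Analysis set.** The Statistical analysis section states: "The primary analysis will use an intention-to-treat (ITT) analysis". The abstract adds: "All enrolled patients will be included in the intention-to-treat analysis". The article names no other analysis set for the primary endpoint.
- **Test.** The Sample size calculation section describes a "sample size calculation for a one-proportion non-inferiority test". It says "it is expected that the 3 year iDFS in patients undergoing SLNB is about 90" per cent, and continues: "We set the non-inferiority margin at 5%, with a power of 80%, a significance level (α) of 0.05 and a 95% CI".
- **Intervention.** Under Trial design and setting, patients have breast surgery "without axillary surgery, with a postoperative follow-up of 3 years". Under Postoperative radiotherapy, the target area leaves out the axilla.
- **After leaving.** Under Clinical intervention and follow-up, and again under Missing data and dropouts, patients who discontinue or withdraw for any reason "can be treated with disease-specific therapies, including supplemental SLNB, ALND, radiotherapy and other therapies as appropriate, after obtaining informed consent".
- **Data of those who leave.** Data collection and management stops collection once consent is withdrawn but retains what was collected before. Consent or assent removes complete withdrawals from the final analysis. Missing data and dropouts carries the last observation forward to protect the ITT analysis.

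**The concern.** The result is meant to speak to the oncological safety of leaving the axilla alone. A patient who has SLNB or ALND before any iDFS event has received the reference care or more, yet in an all-enrolled ITT analysis is counted under omission.

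In a superiority trial such mixing usually works against the claim. In a non-inferiority question it works for it, because it draws the observed result towards that of the reference treatment. Here the bound is fixed and there is no concurrent arm, so nothing in the data would show the dilution.

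The article's own Introduction supports the direction: it credits axillary surgery with lowering axillary recurrence through local control and calls axillary radiotherapy effective too. Regional recurrence, a component of iDFS and a secondary endpoint, is the outcome most exposed. A positive result is also the stated trigger for a phase III trial.

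**Working it through.** **1. The plan's own figure.** The inputs, from the Sample size calculation section, are reference iDFS 0.90, margin 0.05 (so bound p0 = 0.90 − 0.05 = 0.85), expected p1 = 0.90, power 0.80, α = 0.05 (sidedness not stated) and 10% dropout. With a one-sample score test at one-sided 0.05:

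n = [1.645·√(0.85·0.15) + 0.842·√(0.90·0.10)]² / 0.05² = 282.1

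282.1 × 1.1 = 310.3, which rounds up to 311. Dividing 283 by 0.9 instead gives 315. A Wald form at one-sided 0.025 gives n = 282.6, and 282.6 × 1.1 = 310.8, again 311. This agrees with the article: "Considering a 10% dropout rate, PASS software calculated the required sample size to be 311 patients". The sample size is not at issue here.

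**2. Who is affected.** All of these must hold: the patient leaves the omission strategy, has the axilla treated, has had no iDFS event before that treatment, and remains in the analysed set. Treatment given for a recurrence follows an event already counted and dilutes nothing.

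**3. Effect on the test.** Let c be the share so treated. Take true iDFS under omission to be exactly at the bound, 0.85. Give treated patients the plan's own reference rate, 0.90. Then

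p(c) = 0.85·(1 − c) + 0.90·c

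For the ITT set of 311, the exact binomial test at one-sided 0.05 succeeds with at least 275 event-free (88.4%). At one-sided 0.025 it needs at least 277 (89.1%). Outcomes are taken as complete at 3 years. Neither c nor the outcome of treated patients is in the documents; both are assumptions.

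| c (assumed) | p(c) | False claim, one-sided 0.05 | False claim, one-sided 0.025 |
|---|---|---|---|
| 0 | 0.8500 | 5.0% | 2.3% |
| 2% | 0.8510 | 5.5% | 2.6% |
| 5% | 0.8525 | 6.4% | 3.1% |
| 10% | 0.8550 | 8.0% | 4.0% |

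If treated patients had 95% iDFS, the one-sided 0.05 column would read 8.0% at c = 5% and 12.3% at c = 10%.

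In events the shift is small: 311 × 0.0025 = 0.8 fewer expected events at c = 5%, and 311 × 0.005 = 1.6 fewer at c = 10%, against 311 × 0.15 = 46.7 expected.

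A 20% share gives 12.3% (treated patients at 90%), but that is twice the total dropout the plan expects, so it is not a planning case.

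**4. The withdrawal rules side by side.** The abstract puts all enrolled patients in the ITT analysis, and Missing data and dropouts carries observations forward to keep it whole. Consent or assent takes complete withdrawals out. Data collection and management retains their earlier data. These cannot all be followed.

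**The case against.** A reader might infer that every patient with later axillary treatment is counted as evidence that omission is safe. The documents do not support that. The permission is written for patients leaving the trial, not as an in-trial crossover. Patients who withdraw consent have no later data, and complete withdrawals are removed. What stands is a narrower group: the text names discontinuation beside withdrawal, and nothing removes a patient who stops the strategy without withdrawing.

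A reader might also infer that naming ITT, or naming no per-protocol set, is an error. It is neither. ITT is a proper analysis of a strategy of initial omission, and a supportive analysis may stand in a full protocol or SAP not shown here. The point rests on what is written: later axillary treatment is allowed, all enrolled patients are analysed together, and the conclusion is to be about omission.

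Three further objections have force:

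- The size is hypothetical, and the bias arises only if treated patients do better than untreated ones. The permission also does not say that the radiotherapy is axillary.
- The effect should be judged on all 311. On 280 (311 less 10% dropout) the same 5% and 10% shares give 4.5% and 5.7%, from a discrete-test size of 3.6%. But 280 is not the ITT set.
- A per-protocol set defined by later treatment can itself be biased. If those treated are at higher risk, excluding them flatters omission. That rules out replacing ITT with per-protocol. It does not count against requiring both, since a rule that needs two analyses to agree can never make a false claim more likely than ITT alone.

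**Conclusion.** The concern holds in limited form. The plan allows axillary treatment after discontinuation and rests its non-inferiority conclusion on ITT of all enrolled patients. Those treated before an iDFS event and still analysed therefore move the result towards success.

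The true size is unknown. Under the assumptions shown (a 5% or 10% share, 90% against 85% iDFS, all 311 analysed, one-sided 5%), the false-claim rate rises from 5.0% to 6.4% or 8.0%. This is modest, and it would be negligible if few patients take this route. It should still be settled before analysis, because a single-arm result cannot be disentangled afterwards if the treatment was not recorded. Separately, the withdrawal rules contradict the all-enrolled ITT set and must be reconciled.

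**What to change.** No view is taken on whether or when supplemental axillary treatment should be given. The changes concern data and analysis:

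1. Keep ITT as the primary analysis, and reconcile the statements on withdrawn patients so that one rule defines the set.
2. Keep following patients who stop the strategy unless they withdraw consent to data collection.
3. Record the date, reason and nodal pathology of any supplemental axillary treatment.
4. Prespecify a per-protocol analysis of eligible patients with no axillary surgery or axillary radiotherapy before a first iDFS event. Add a sensitivity analysis that censors at such treatment, because exclusion by later treatment can select lower-risk patients.
5. Claim non-inferiority of omission only if ITT and per-protocol agree.
6. Report how often supplemental axillary treatment occurred, and regional recurrence with and without these patients.

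The cost is a little power from the smaller per-protocol set and the double requirement, some added analysis, and one extra data item, since the schedule in Table 1 has no line for supplemental axillary treatment. If a full protocol or SAP already covers these points, the sponsor need only confirm it.
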